## Abstract

**Background:**

Knee osteoarthritis (KOA) is a chronic degenerative disease characterized primarily by pain and joint dysfunction, especially during level and stair walking. Although traditionally classified as a peripheral joint disease, emerging evidence implicates central nervous system (CNS) abnormality in KOA pathogenesis. Our previous studies found that KOA patients showed decreased activation in sensory-motor cortex during isolated joint movements. However, it is not yet clear how brain activation patterns change during level and stair walking. Therefore, this study will investigate the sensory-motor cortex activation in KOA patients during different walking environments, providing evidence for potential targets for KOA central interventions.

**Methods:**

This study is designed as a cross-sectional observation, aiming to recruit 20 KOA patients and 20 demographically similar healthy controls (HC). Functional near-infrared spectroscopy (fNIRS) is utilized to assess the hemodynamic responses in the cerebral cortex within the specified regions of interest (ROIs), including the primary somatosensory cortex (S1), primary motor cortex (M1), and somatosensory association cortex (SAC). These measurements will be taken during three motor tasks: level walking, ascending stairs, and descending stairs. Simultaneously, surface electromyography (sEMG) is employed to measure muscle activity of the key muscle groups around the knee joint. The VAS and the WOMAC used to evaluate pain and functional symptoms in KOA patients, respectively. Subsequently, the potential correlations between cerebral hemodynamics changes within ROIs and clinical indicators are analyzed.

**Discussion:**

This study, based on “differential activation of the sensory-motor cortex under movement,” innovatively observes the relationship between pain and functional impairment in KOA patients and activation levels in specific brain regions across different motor environments. This not only provides a basis for early prediction of KOA onset but also offers potential targets for clinical interventions in KOA. Ultimately, the results of this study may open new perspectives for the rehabilitation of chronic musculoskeletal diseases.

## 1 Introduction

Knee osteoarthritis (KOA) is a common chronic joint disease characterized by pain and functional limitations (Jang et al., 2021; Katz et al., 2021; Alves-Simões, 2022). Epidemiological studies indicate that the incidence of knee osteoarthritis significantly increases with age, particularly among the elderly over 65, where the prevalence rate can reach 50%–60% (Bryk and Starowicz, 2021). With disease progression, it not only severely reduces the quality of life for patients but also exerts a heavy economic burden on society (Wood et al., 2013; Cohen et al., 2021). Despite the fact that there are currently multiple treatment approaches for KOA, including pharmacological treatment, physical therapy and surgical intervention, these methods frequently have limitations such as drug-induced toxic effects on other organ systems (e.g., gastrointestinal, cardiovascular, and renal systems), variable efficacy, and long-term financial burdens associated with chronic medication use or postoperative rehabilitation (Michael et al., 2010; Mahmoudian et al., 2021; Gelber, 2024). Hence, in-depth studies on the pathogenesis of KOA and its related factors (e.g., neurological factors) are particularly crucial, which will facilitate our development of more effective treatment strategies (Primorac et al., 2020; Du et al., 2023).

At present, studies for KOA mainly concentrates on the clinical characteristics and pathophysiological changes, but relatively less attention is placed on changes in the central nervous system (Dell’Isola et al., 2016; Yang et al., 2023). With the advancement of research, researchers have gradually realized that KOA patients had changes in brain structure and function, and these changes are closely related to pain perception and dysfunction (Shanahan et al., 2015; Liu et al., 2019; Barroso et al., 2020; Kang et al., 2021; Cheng et al., 2022). Studies have demonstrated that significant changes have occurred in the brain morphology of patients with KOA, including reductions in gray matter volume and changes in white matter integrity and static activity (Kang et al., 2021; Cheng et al., 2022). A magnetic resonance imaging (MRI) study using voxel-based morphometry (a neuroimaging technique for detecting structural brain changes) discovered that KOA patients had a decreased gray matter in regions related to pain processing and emotion regulation, such as the anterior cingulate cortex and insula (Kang et al., 2021). These changes might be associated with the persistence of chronic pain and modifications in the mechanisms of pain perception and regulation. The same study using MRI found that significant alterations occurred in the activation sites of the motor cortex in patients with KOA during the execution of isometric motion, which were linked to modifications in motor functions and behaviors (Shanahan et al., 2015). The authors suggest that these changes could be a significant contributing factor to the impaired motor performance observed in patients with KOA. Furthermore, another study using electroencephalogram (EEG) revealed distinct event-related desynchronization (decreased cortical oscillations reflecting neural activation) and synchronization (increased rhythmic activity associated with inhibitory processes) patterns in the EEG of KOA patients performing motor imagery tasks compared to healthy individuals (Marques et al., 2023). These findings imply that the brain function of KOA patients may be affected by chronic pain and functional limitations, leading to decreased motor control and sensory function. Nevertheless, existing research focusing solely on the resting state have failed to capture the brain activation patterns associated with dynamic physical movement, which are essential for a comprehensive perspective on KOA.

During movement execution, joints are subjected to greater loads and pressures, requiring a higher degree of sensorimotor integration, which may trigger more pronounced pain perception and changes in the activation of related functional brain regions (Marriott et al., 2019; Hutchison et al., 2022; Pan et al., 2024). Investigating these activation changes not only enhances our understanding of the neural mechanisms of pain processing, but also reveal possible impairments in patients’ motor performance. In order to study the activation changes in brain regions under dynamic knee movements, our research group previously employed functional near-infrared spectroscopy (fNIRS) to observe the activation of sensory-motor related brain regions in KOA patients during isokinetic knee movement and ultimately found that these brain regions were in a state of low activation (Yang et al., 2024). Nevertheless, the aforementioned study was limited to observations in specific environments, which differed significantly from the real-life daily activity environment. Bishnoi’s investigation focused on understanding how confronting unexpected challenges during gait—specifically, perturbation walking—affects prefrontal cortical activation in older women diagnosed with osteoarthritis (Bishnoi et al., 2024). The study found that prefrontal cortex activation increased significantly during perturbation walking compared to comfort walking, and this increase was more significant in healthy elderly women. However, the author only observed activation of the prefrontal cortex, and this observation was limited to the treadmill, which was different from daily walking. To clarify the above circumstances, our research group intends to further understand the activation patterns of the sensorimotor cortex of KOA patients in a real walking environment, including level walking and stair walking. Dynamic loading during gait and stair walking, characterized by high volume and frequency, is a fundamental aspect of human daily activities (Andriacchi et al., 2009). Notably, functional mobility limitations are frequently reported as primary challenging aspects of their condition among patients with KOA (Katz et al., 2021).

This study adopts a cross-sectional research design and utilized fNIRS to investigate brain activities changes in KOA patients under different movement contexts. The specific objective is to analyze the correlation between these changes and the patients’ pain and functional scores. This will provide a more powerful theoretical basis for the central intervention programs for KOA patients.

## 2 Materials and methods

### 2.1 Study design

This study will adopt a cross-sectional study design comparing the differences in brain activation patterns and lower limb muscle activation patterns between KOA patients and Healthy controls (HC) during level and stair walking, and investigating their relationship with pain degree and dysfunction in KOA patients. A brief flowchart of the entire study is shown in Figure 1. The study protocol’s adherence to the STROBE checklist for cross-sectional studies signifies that all aspects of study design, execution, and reporting will follow established best practices for observational research (von Elm et al., 2008). The Ethics Committee of Shanghai Seventh People’s Hospital approved the study (2024-7th-HIRB-098), and it is registered with the Chinese Clinical Trial Registry (ChiCTR2400092793).

**FIGURE 1 F1:**
[figure not shown]
A brief flowchart of the entire study. KOA, knee osteoarthritis; VAS, visual analog scale; WOMAC, Western Ontario and McMaster Universities Osteoarthritis Index; fNIRS, functional near-infrared spectroscopy; sEMG, surface electromyography.

### 2.2 Sample size calculation

The sample size for this study was determined through a priori power analysis performed using G*Power software (version 3.1.9.7) (Faul et al., 2007). Based on previous research, the study employed an Analysis of Variance (ANOVA) with repeated measures in the calculations. We expected an effect size of 0.40, an alpha error of 0.05 and a power level (1–β) of 0.20. The analysis indicated that at least 36 participants would be necessary to achieve an adequate cohort size for the study. Taking into account the participant dropouts rate 10%, the final sample size for this study was set at 40 individuals, with 20 participants allocated to each group. This sample size is considered adequate to generate reliable and valid outcomes for the research.

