### 2.8 Statistical analysis

The statistical analysis of this study covers clinical indicators, muscle and brain activation. Statistical analysis will be conducted on clinical indicators and muscle activation using SPSS 21.0 Software (IBM Corporation, New York, United States). Continuous variables with normal distribution will be presented as mean ± standard deviation, while non-normally distributed variables will be shown as median and quartiles. Categorical variables will be reported as frequency. The normality test will be performed using Shapiro-Wilk test. An independent *t*-test is applied when demographic data follow a normal distribution. Otherwise, the Mann–Whitney’s U test will be applied. The Chi-square test will be used to compare sex. Muscle activation in different groups (KOA and HC) and tasks (level walking, ascending stairs, and descending stairs) will be analyzed using mixed ANOVA or non-parametric tests (for non-normality). For brain activation analyses, a flexible factorial design (FFD) in SPM will be employed to construct a mixed-effects model including groups (inter-subject factors) and tasks (intra-subject factors) to evaluate group main effects, task main effects and their interactions. SPM will be thresholded with cluster-level false discovery rate (FDR) correction (*p* < 0.05). To explore the correlation between brain activation (HbO concentration and β value) and clinical indicators (VAS and WOMAC) in KOA patients, a multiple linear regression analysis will be performed to calculate the Pearson correlation coefficient and RMS value. Additionally, a non-linear regression prediction based on the random forest algorithm will be used to assess the importance of regression between various brain regions, muscle characteristics, and clinical indicators. All statistical tests will use a significance level of 0.05, with corrections for multiple comparisons made using the Bonferroni adjustment.

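### The sample-size paragraph reports β = 0.20 as the power, and the 36 participants reproduce at 80% power for one unadjusted test, with no allowance for the Bonferroni adjustment stated later

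*Protocol article*

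**What the plan says.** Section 2.2 of the protocol article describes an a priori calculation in G*Power. The method is given as "the study employed an Analysis of Variance (ANOVA) with repeated measures in the calculations", and the inputs as "We expected an effect size of 0.40, an alpha error of 0.05 and a power level (1–β) of 0.20". The result is "The analysis indicated that at least 36 participants would be necessary", raised to 40 (20 per group) for 10% dropout. The paragraph does not say whether the group effect, the task effect or their interaction was powered. It also omits the number of measurements and the correlation between them.

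Section 2.8 contains two multiplicity statements. For the brain-activation model, "SPM will be thresholded with cluster-level false discovery rate (FDR) correction" at p < 0.05. The closing sentence then sets 0.05 for all tests, "with corrections for multiple comparisons made using the Bonferroni adjustment". It gives neither the family nor the number of tests. Section 2.5 lists six regions of interest (ROIs) and section 2.6 lists seven muscles.

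**The concern.** The label (1–β) turns 0.20 into a claim of 20% power. Taken literally, the study's only sample-size justification says it would miss the assumed effect four times in five, and that input cannot produce 36. A reader cannot tell from the paragraph what power the study was designed to have.

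The second problem is the link to the analysis. The calculation uses "an alpha error of 0.05", the level for one test, while section 2.8 announces a Bonferroni adjustment. For any outcome to which that adjustment applies, each test is run at a stricter level than the one the sample size was built on. The power for that outcome is then lower than intended and is reported nowhere.

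**Working it through.** **Inputs from the documents.** Effect size 0.40 (taken as Cohen's f), alpha 0.05, stated power 0.20, N = 36, dropout 10% and final N = 40 (all section 2.2); 2 groups and 3 tasks (section 2.8); six ROIs (section 2.5); seven muscles (section 2.6).

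**Assumptions.** The correlation between measurements is ρ = 0.5, the G*Power default, which the article does not state. The powered effect is the between-groups effect, because that choice returns 36.

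**Formula.** For the between-groups effect in repeated-measures ANOVA with m measurements, the noncentrality is λ = f² × N × m / (1 + (m − 1)ρ), with 1 and N − 2 degrees of freedom. With m = 3 and ρ = 0.5 this is λ = 0.16 × N × 3 / 2 = 0.24 × N.

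**Step 1: reproduce the 36 at alpha 0.05.**

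| N | λ | Power |
|---|---|---|
| 8 | 1.92 | 21.6% |
| 34 | 8.16 | 79.1% |
| 36 | 8.64 | 81.5% |
| 40 | 9.60 | 85.5% |

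The smallest even N is 8 for 20% power and 36 for 80% power. At 90% power it would be 46. Among the repeated-measures variants tried at 20% power (group, task and interaction effects; several effect-size conventions and correlations), none needed more than 10. The dropout step is correct: 36 / 0.9 = 40.

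**Step 2: apply Bonferroni to the same group effect (ρ = 0.5).** The family of three is illustrative. Six and seven are the numbers of ROIs and muscles.

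| Family | Alpha per test | N = 36 | N = 40 |
|---|---|---|---|
| 1 test | 0.05 | 81.5% | 85.5% |
| 3 tests | 0.0167 | 66% | 72% |
| 6 tests (ROIs) | 0.0083 | 56% | 62% |
| 7 tests (muscles) | 0.0071 | 54% | 60% |

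**Step 3: sensitivity to the unstated correlation (six tests, N = 36).** At ρ = 0.3, λ = 17.28 / 1.6 = 10.8 and power is 68%. At ρ = 0.7, λ = 17.28 / 2.4 = 7.2 and power is 46%.

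**Step 4: sensitivity to the unstated effect.** For the group-by-task interaction under G*Power's default convention, λ = f² × N × m / (1 − ρ). That needs only 12 participants for 80% power at alpha 0.05, and at N = 36 power stays above 99% even at 0.05/6. Under the SPSS-type effect-size convention the interaction needs 34, close to the reported 36.

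**The case against.** The label error leaves the design unchanged: 36 and 40 are right for 80% power, so one figure in one sentence needs correcting. That stands, and it also rules out reading the sentence as evidence that the study really has 20% power.

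A reader might also infer that the analysis as planned has only about 56% power. The documents do not support this. The 56% requires a Bonferroni family of exactly six, applied to brain data that section 2.8 assigns to cluster-level FDR, for the group effect, at a correlation of 0.5, with 36 completers. The article fixes none of the conditions on family, effect or correlation, and the interaction under the default convention would be amply powered.

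Nor is it established that two rules govern the brain outcome. An ordinary reading is that FDR is the specific rule for the SPM maps and Bonferroni the general rule for the SPSS analyses. The wording is loose enough to need clarifying, but it is not a proven contradiction.

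Finally, the settings that return 36 are back-calculated. The authors should report what they entered, and G*Power settings and family definitions may well sit in the full protocol or SAP. That excuses the omissions. It does not excuse a wrong power figure, or an alpha that takes no account of an adjustment announced in the same article.

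**Conclusion.** The concern holds in a limited form. The stated power is wrong as written: "a power level (1–β) of 0.20" should read 0.80. The 36 reproduces exactly at 80% power with alpha 0.05, given a between-groups effect, three measurements and a correlation of 0.5.

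The calculation covers a single unadjusted test. Wherever Bonferroni is applied to the group effect under those settings, power drops below 80%. The muscle outcomes show that this does not depend on the FDR question: section 2.8 assigns them to mixed ANOVA or non-parametric tests, where only the Bonferroni sentence can apply, and a seven-muscle family would give 54% at 36 completers. All the reduced figures remain conditional on the family, the effect and the correlation, and none should be quoted as the power of the study.

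**What to change.** 1. In section 2.2, correct the power (1–β) to 0.80.
2. State the effect, the number of measurements and the correlation actually entered in G*Power, taken from the original run and not inferred from the 36.
3. Say that the 80% applies to a single test at alpha 0.05. For any outcome family to which Bonferroni applies, give the number of tests and restate the power at the adjusted alpha.
4. In section 2.8, state that cluster-level FDR governs the SPM brain model and Bonferroni the other tests, or the reverse, so that one rule applies to each outcome.

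These are changes of wording and reporting. No extra participants are needed. The cost is a less favourable stated power for any Bonferroni-adjusted outcome.

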### 2.3 Participants

The study will be conducted in the Department of Rehabilitation at Shanghai Seventh People’s Hospital from August to September 2025. KOA patients will be recruited from the hospital’s outpatient clinics or nearby community health centers through posters displayed by doctors or therapists. Participants who express their interest in the study will be evaluated for eligibility to determine whether they meet the inclusion criteria for this research. At the same time, researchers will obtain consent in accordance with the principle of informed consent to confirm the voluntariness of the participants. The inclusion criteria: (1) age from 50 to 75 years; (2) KOA diagnosis following the American College of Rheumatology’s clinical criteria; (3) clinical and radiological signs in the right knee only; (4) Kellgren-Lawrence grade II or III; (4) chronic pain (present for no less than 3 months) exceeds 30 out of 100. The exclusion criteria: (1) a history of severe knee injury or rheumatic disorders; (2) a history of cerebrovascular disease, mental illness or brain metal implantation; (3) drug/alcohol abuse; (4) cognitive impairment or failure to cooperate. HC will be recruited from communities around the hospital via word-of-mouth and advertisements, who have no history of diseases affecting joints and brain. All individuals need to have a right lower limb dominance, determined by their kicking preference (Willems and Ponte, 2012). Before the study is carried out, all subjects are required to complete a written informed consent form in accordance with ethical review requirements.

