### 2.4 Procedure

Before the experiment, the demographic data of all subjects will be first collected. We then explained the experimental process, test actions, and precautions to the participants. Adequate time will be provided for them to acclimate to the experimental process, ensuring a comprehensive understanding of the experimental requirements. Subsequently, fNIRS equipment and sEMG sensors will be affixed to each participant.

The experimental protocol consists of three distinct motor tasks: level walking, ascending stairs, and descending stairs. Participants will perform three tasks in a random order, with each task being repeated three times. There will be a 5 min interval between tests to allow participants to rest adequately and ensure that the fNIRS spectral signals of each test return to the baseline. Tests will be conducted on the KOA patients first, followed by the healthy controls. During the level walking, the patients will be instructed to walk at a normal, comfortable self-selected speed (SSS) for 30 s each time, with SSS defined as the average velocity from three timed baseline walks. The stair program evaluation will use standardized stairs under the same SSS conditions, maintaining consistent handrail non-use protocol across groups. The staircase consisted of 10 steps, with each step having a height of 12 cm, conforming to the standard specification for steps in China. To mitigate speed-related confounding effects, healthy controls will be pace-matched to the patient cohort’s average speed under the same conditions. A schematic overview of the experimental protocol is depicted in Figure 2. During the test, if the participant experiences any discomfort (e.g., dizziness, or falls), the testing will be immediately stopped and undergo medical evaluation of whether to continue.

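### Controls are promised to be demographically similar, but no matching rule is stated for them and the 50–75 age range is not clearly extended to them, so the KOA-versus-control contrasts can carry an age effect

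*Protocol article*

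**What the plan says.** - **Abstract, Methods.** The aim is 20 KOA patients and "20 demographically similar healthy controls (HC").
- **Section 2.3, the criteria list.** It begins "The inclusion criteria: (1) age from 50 to 75 years; (2) KOA diagnosis following the American College of Rheumatology’s clinical criteria". The remaining inclusion items are right-knee signs, Kellgren-Lawrence grade and chronic pain. From item 2 on, only a KOA patient can qualify.
- **Section 2.3, controls.** They have a separate sentence: "HC will be recruited from communities around the hospital via word-of-mouth and advertisements, who have no history of diseases affecting joints and brain". No age, sex or matching condition is given there.
- **Section 2.3, both groups.** The one entry characteristic stated for everybody is limb dominance: "All individuals need to have a right lower limb dominance, determined by their kicking preference".
- **Section 2.4.** Patients are tested first and controls afterwards. The only matching described is of walking speed: "healthy controls will be pace-matched to the patient" cohort's average. Demographic data are collected from all subjects.
- **Section 2.8.** Demographics are compared by t-test or Mann–Whitney test, and sex by chi-square. The muscle and brain activation models contain group and task. No covariate is named.
- **Introduction.** It states that "the incidence of knee osteoarthritis significantly increases with age" and gives a prevalence of up to 50–60% in people over 65.

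**The concern.** In a two-group cross-sectional comparison, the way controls are chosen decides whether a group difference can be read as a disease difference. Here the abstract states the goal of similarity, but the stated selection rule does not produce it and pulls the other way on age. People with no history of joint disease are, on the document's own account of KOA, more likely to be found at the younger end of any age range.

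Two later steps might be expected to catch or remove the imbalance. The demographic tests have low power for a gap of a few years at 20 per group, so a non-significant p-value could be read as confirming similarity. The group-by-task models as described make no adjustment. If HbO, β values or sEMG measures vary with age, part of the KOA-versus-control difference would then be an age difference.

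**Working it through.** **Inputs from the protocol.** Section 2.2 gives at least 36 participants and 10% dropout: 36 / (1 − 0.10) = 40, so 20 per group. That reproduces the plan's figure. Significance level 0.05. Patient age range 50–75. Prevalence 50–60% over 65. The protocol gives no figure for age imbalance, so the rest is an illustration on stated assumptions.

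**Assumptions, not in the protocol.** Source-population ages are uniform over 50–75. KOA prevalence rises linearly from p₀ at 50 to 0.60 at 75, with p₀ = 0.10, 0.20 or 0.30. The within-group correlation r between age and the subject's mean outcome is 0.3 to 0.5. There is no true KOA effect.

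**Step 1: age gap if controls are also 50–75.** Patients are drawn in proportion to prevalence and controls in proportion to one minus prevalence. With q = 0.60 − p₀:

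- patient mean age = 50 + 25 × (p₀/2 + q/3) / ((p₀ + 0.60)/2)
- control mean age = 50 + 25 × ((1 − p₀)/2 − q/3) / (1 − (p₀ + 0.60)/2)

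For p₀ = 0.30, patients: 50 + 25 × 0.25/0.45 = 63.89. Controls: 50 + 25 × 0.25/0.55 = 61.36. The gap is 2.53 years. The pooled SD under the same densities is 7.10 years, so d = 2.53/7.10 = 0.36.

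**Step 2: power of the planned t-test on age.** Two-sided noncentral t, 38 degrees of freedom, critical value 2.024, noncentrality d × √(20/2).

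**Step 3: false group effect.** Unadjusted, the group contrast shifts by r × d in outcome SD units. The type I error comes from the same noncentral t with r × d in place of d.

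| p₀ at age 50 | Patient mean | Control mean | Gap (years) | d | Power of age test | Type I error, r = 0.3 | Type I error, r = 0.5 |
|---|---|---|---|---|---|---|---|
| 0.30 | 63.89 | 61.36 | 2.53 | 0.36 | 0.195 | 6.2% | 8.5% |
| 0.20 | 64.58 | 61.11 | 3.47 | 0.50 | 0.334 | 7.4% | 11.9% |
| 0.10 | 65.48 | 60.90 | 4.58 | 0.67 | 0.545 | 9.5% | 17.9% |

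The false effect itself runs from 0.3 × 0.355 = 0.11 SD to 0.5 × 0.672 = 0.34 SD.

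**Step 4: cross-check with a fixed SD.** With an assumed age SD of 6.5 years, the baseline test has power 30% for a 3-year gap, 48% for 4 years and 66% for 5 years. A 3–5 year gap would therefore pass unnoticed 34–70% of the time.

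**Step 5: can adjustment help?** The overlap of the two age distributions (the area under the smaller density at each age) is 85%, 79% and 73% for the three rows. That is ample for a covariate to work.

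The type I error figures are for one unadjusted two-sided contrast of subject means at 5%. They are not the error rate of the FDR-thresholded brain map or of the Bonferroni-corrected family.

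**The case against.** The best defence is that this is a condensed article. The intent is stated in the abstract, and pairing rules and tolerances commonly sit in a full protocol that is not shown. The criteria list in section 2.3 is not labelled as applying to patients only, and the limitations paragraph describes the study as confined to a specific age range. A reader may fairly take 50–75 to cover controls. That stands, so it would be wrong to say that controls have no age limit. It does not answer the point, because the calculation above already gives controls the 50–75 range and a gap remains. Section 2.3 also does more than omit detail: it states how controls qualify, and that rule does not lead to the promised similarity.

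Four stronger readings are tempting, and the documents do not support them:

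- **A wider control age range.** Supposing controls from 45 gives gaps of 5.4–7.6 years and type I error of 10–34%, but nothing in the text suggests that range. The age test would also often flag such gaps (57–88% power).
- **Groups too far apart for a covariate to help.** The overlap in step 5 contradicts this.
- **Confounding by body mass.** The documents do not mention BMI or body weight and give no figure for an imbalance. Any assumed kilogram difference would be invented, and no link to HbO or sEMG is given.
- **Damage to the whole study.** The specific objective in the Introduction, correlation of activation with pain and function scores, is analysed within KOA patients. Control recruitment does not touch it.

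It also stands that the low end is small: 6% against 5%.

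**Conclusion.** The point holds for the KOA-versus-control contrasts. Similarity is promised, the stated control rule tends towards younger people, the planned tests would often miss a gap of a few years, and the models as described do not adjust for it.

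The size is modest to moderate: a gap of about 2.5–4.6 years, detected with about 20–55% power, and type I error of about 6–18% for a single contrast. These figures rest on an assumed prevalence curve, uniform ages and an age–activation correlation of 0.3–0.5. Only the direction, KOA rising with age, and the 50–60% prevalence over 65 come from the document. This is a risk of confounding by age, not a demonstrated bias. It is worth correcting before controls are recruited, because the remedy is cheap.

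**What to change.** - **Section 2.3:** state that the 50–75 range applies to controls. Frequency-match controls to the enrolled patients on age band and sex. Patients are tested first (section 2.4), so their distribution can be known when controls are selected.
- **Section 2.8:** report balance as standardised differences and do not infer similarity from non-significant p-values. Include age as a covariate in the group contrasts for brain and muscle activation.
- **Optional:** record and describe BMI with the demographic data.

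The cost is a sentence or two in each section and one model term. Some volunteer controls will be declined, and control recruitment may be slightly slower. No added participants are needed.
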